## Abstract

**Background:**

High tibial osteotomy is a common procedure to treat symptomatic osteoarthritis of the medial compartment of the knee with varus alignment. This is achieved by overcorrecting the varus alignment to 2-6° of valgus. Various high tibial osteotomy techniques are currently used to this end. Common procedures are medial opening wedge and lateral closing wedge tibial osteotomies. The lateral closing wedge technique is a primary stable correction with a high rate of consolidation, but has the disadvantage of bone loss and change in tibial condylar offset. The medial opening wedge technique does not result in any bone loss but needs to be fixated with a plate and may cause tibial slope and medial collateral ligament tightening. A relatively new technique, the combined valgus high tibial osteotomy, claims to include the advantages of both techniques without bone loss. Aim of this prospective randomized trial is to compare the lateral closing wedge with the combined wedge osteotomy in patients with symptomatic varus osteoarthritis of the knee.

**Methods/design:**

A group of 110 patients with osteoarthritis of the medial compartment of the knee with 6-12° varus malalignment over 18 years of age are recruited to participate a randomized controlled trial. Patients are randomized to undergo a high tibial osteotomy, with either a lateral closing wedge technique or a combined wedge osteotomy technique. Primary outcome measure is achievement of an overcorrection of 4° valgus after one year of surgery, assessed by measuring the hip-knee-ankle angle. Secondary objectives are radiological scores and anatomical changes after high tibial osteotomy; pain, functional scores and quality of life will also be compared.

**Discussion:**

Combined high tibial osteotomy modification avoids metaphyseal tibial bone loss, decreasing transposition of the tibial condyle and shortening of the patellar tendon after osteotomy, even in case of great correction. The clinical results of the combined wedge osteotomy technique are very promising. Hypothesis is that the combined wedge osteotomy technique will achieve more accurate overcorrection of varus malalignment with fewer anatomical changes of the proximal tibia after one year.

**Trial registration:**

Dutch Trial Registry (Netherlands trial register): NTR3898.

## Background

Knee osteoarthritis (OA) is the most common joint disorder, and the lifetime risk of developing symptomatic knee OA has been estimated to be around 45% [1,2]. Many patients present with unicompartmental knee OA, which is generally caused by a mechanical problem and may lead to knee malalignment [3]. Knee malalignment is a determinant of load distribution, and is associated with OA progression [4].

Alterations in the mechanical stresses on the knee joint tissues improves symptoms and reduces the risk of developing radiographic knee OA [5]. Valgus-producing high tibial osteotomy (HTO) does correct varus malalignment and is an accepted treatment for medial unicompartmental knee OA in active patients [6]. Aim of the HTO procedure is to offload the medial compartment by overcorrecting the varus malalignment to 2-6° of valgus [7-11].

The two most commonly used surgical techniques for HTO are lateral closing wedge HTO (LCW) and medial opening wedge HTO (MOW) with internal fixation, which has gained popularity in recent years. In both techniques the goal is to achieve and maintain adequate correction of malalignment of the knee joint. In the lateral closing wedge technique a wedge of bone with the base on the lateral side is removed from the proximal tibia, producing valgus. A fibular osteotomy or release of the proximal tibiofibular joint is necessary. After LCW, lateral tibial metaphyseal bone loss may occur and can lead to considerable lateral overhang of the tibial plateau, producing changes in tibiocondylar offset. MOW does not cause any bone loss but needs stable plate fixation with possible tibial slope changes, medial collateral ligament tightening and patella baja [12]. There are no differences between LCW and MOW in frequency and type of complications [13].

A relatively new HTO technique, the combined valgus-producing high tibial osteotomy (CWO), claims to include the advantages of both the LCW and the MOW techniques for HTO. This HTO modification avoids metaphyseal tibial bone loss, decreasing transposition of the tibial condyle and shortening of the patellar tendon after osteotomy, even in cases of great correction [14]. The aim of this prospective randomized trial (RCT) is to compare LCW with CWO in patients eligible for HTO who have varus alignment up to 12°. Hypothesis is that the CWO technique will achieve more accurate overcorrection of varus malalignment with fewer anatomical changes of the proximal tibia after one year.

## Methods/design

### Study design

The study design is a randomized controlled trial. Patients will be allocated to two groups: HTO with CWO technique or HTO with LCW technique. The study will be conducted at the Orthopedic Department of Martini Hospital in Groningen. The study design, procedures, protocols and informed consent are approved by the local Medical Ethical Committee. The trial is registered in the Netherlands Trial Registry (NTR3898).

### Study population

Patients visiting the outpatient clinic of the Orthopedic Department who have an indication to undergo HTO because of osteoarthritis of the medial compartment of the knee with varus alignment will be included if they meet the following criteria: radiologically confirmed medial compartment osteoarthritis, medial joint pain, 6-12° varus alignment and age 18 and older. Exclusion criteria are: symptomatic osteoarthritis of the lateral compartment, rheumatoid arthritis, range of motion of the knee joint under 100°, flexion contracture more than 10°, grade 3 collateral laxity (Insall), history of fracture or previous open operation of the lower extremity, mental incapacity, or inability to fill in the questionnaires in Dutch.

### Interventions

After randomization patients will undergo either a CWO HTO or a LCW HTO; all patients will be operated on by one of two orthopedic surgeons, both experienced in applying the two techniques so there will be no bias. Preoperative the wedge-correction is calculated aiming on 4° overcorrection.

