### Randomization, blinding and treatment allocation

For randomization a restricted randomization/blocked randomization (2×10 patients in one block) method will be used. The same number of patients will be allocated to each surgical treatment group. Two random allocation sets (for the CWO and the LCW) will be generated by a computer. These allocations are then sealed in consecutively numbered opaque envelopes. Once the patient has given consent to be included in the trial, the HTO technique (CWO or LCW) is randomly assigned by opening the next sealed envelope.

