### Statistics

All data will be analyzed according to an intention-to-treat principle, implying that all patients who are randomized will be included in the analyses, and that they will be analyzed according to the group to which they were allocated. For those patients who will be lost to follow-up or will be re-operated during follow-up, the last available measurement or the last measurement will be forwarded (Last Value Carried Forward technique).

A multivariable linear regression method will be used to analyze the impact of LCW versus CWO HTO on postoperative alignment, posterior tibial slope, patellar height, leg length, VAS, KOOS, walking distance and patients with adverse events at the one-year follow-up. A multivariable logistic regression method will be used for the dichotomous outcome measures. Gender, age and baseline values for HKA angle, VAS knee, KOOS, walking distance, medial osteoarthritis more than joint space loss alone, and concurrent OA of the lateral compartment will be considered as possible confounders and are included in the regression models only if they change the relationship between dependent variable and type of HTO by at least 10%. The SPSS program will be used for the statistical analyses and a p-value of 0.05 is considered statistically significant.

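### Surgeon experience does not establish the absence of bias that the plan claims; operating surgeon should be a prespecified model term and be fixed before the envelope is opened

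*Protocol article*

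**What the plan says.** The protocol article, under Interventions, states that every operation is done by one of two surgeons, "both experienced in applying the two techniques so there will be no bias". Experience is the only safeguard it gives on this point.

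Under Randomization, blinding and treatment allocation, it says that a "restricted randomization/blocked randomization (2×10 patients in one block) method will be used". No stratum is named. After consent, "the HTO technique (CWO or LCW) is randomly assigned by opening the next sealed envelope". The article does not say how or when a patient is assigned to a surgeon.

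Under Statistics, the possible confounders are listed one by one: "Gender, age and baseline values for HKA angle, VAS knee, KOOS, walking distance, medial osteoarthritis more than joint space loss alone", and lateral-compartment OA. Surgeon is not on the list. A listed variable enters a model only if it shifts the estimated technique effect by at least 10%. The examples of potential confounders under Other study parameters do not name the surgeon either.

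**The concern.** The primary outcome is the accuracy of a correction carried out by hand, aimed at 4° valgus. The sample size counts a result of 2-6° as success. The wedge is calculated before surgery, so what remains is largely execution, and two surgeons may differ in that. Experience in both techniques shows that each surgeon can do either operation. It does not show that the two are equally accurate, or that each will do the same proportion of both arms.

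Two consequences need to be kept apart. If surgeon and technique are unrelated by design, a surgeon difference adds noise, and in a particular trial the arms may by chance have different surgeon shares. If the surgeon is picked after the technique is known, the shares can differ systematically, and part of any technique difference would then be a surgeon difference. Under the plan as written, the models would correct for neither, because surgeon is not a candidate covariate.

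**Working it through.** **Inputs from the article.** Success 60% (LCW) versus 85% (CWO), a difference of 25 points; α = 0.05 (taken as two-sided); power 80%; 50 per arm; 110 in total; two surgeons.

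**Inputs assumed, because the article does not give them.** Each surgeon's share of cases, and the difference in success rate between the surgeons. Ranges are shown.

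**1. The plan's own figure.** Pooled two-proportion formula with mean rate 0.725:

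n = [1.96·√(2·0.725·0.275) + 0.842·√(0.60·0.40 + 0.85·0.15)]² / 0.25² ≈ 48.9, so 49 per arm. This agrees with the stated 50; power at 50 per arm is 80.9%. The surgeon question does not alter this calculation.

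**2. Surgeon independent of allocation.** With an even surgeon split and 55 per arm, the SD of the between-arm difference in surgeon share is √(2·0.25/55) = 0.095, or 9.5 points. In simulation the difference exceeds 10 points in 29% of trials and 15 points in about 10%.

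- Error in the estimate = imbalance × surgeon difference. With 15 points of imbalance and an assumed surgeon difference of 20 points: 0.15 × 0.20 = 3 points. The standard error of the planned difference at 50 per arm is √(0.3675/50) = 8.6 points, so this is about a third of one standard error.
- Averaged over trials, the expected bias is zero. Simulated unadjusted type I error at 50 per arm stays between 4.9% and 5.3%, for surgeon differences of 0, 20 and 40 points and surgeon shares of 50% or 70%.
- Imbalance of 20 points or more occurs in 4% to 6% of these simulated trials. Within those trials, type I error is about 7% for a 20-point surgeon difference and 14% for a 40-point one.

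**3. Surgeon chosen with knowledge of the technique (assumed).** Spurious effect = difference in surgeon share between arms × difference in success between surgeons.

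| Surgeon A's share, one arm vs the other | Surgeon difference 10 points | 20 points | 30 points |
|---|---|---|---|
| 60% vs 40% | 2 | 4 | 6 |
| 70% vs 30% | 4 | 8 | 12 |

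The second row is 16% to 48% of the planned 25 points (4/25 to 12/25).

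**4. What adjustment gains or costs.** Simulated at 50 per arm with an even split and a true effect of 25 points, comparing an unadjusted test with a Mantel-Haenszel test stratified by surgeon, which stands in for a surgeon term in the logistic model:

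- Surgeon difference of 20 points (70% vs 50%, assumed): power 81.9% unadjusted, 83.6% stratified; type I error 5.3% and 5.0%.
- No surgeon difference: power 81.8% unadjusted, 81.2% stratified.

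**The case against.** The strongest reply is that randomisation already does the work. Technique is assigned by sealed envelope, so if surgeon is unrelated to allocation the expected bias is zero and the test keeps its size. Chance imbalance is part of the sampling error that the test allows for. This is correct, and a reader who infers that any surgeon imbalance biases the primary comparison goes further than the design supports.

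A reader might also infer that patients will be routed to a surgeon by technique. The article does not say so. Its reference to surgery after randomisation dates the operation, not the choice of surgeon, and a journal article may leave such scheduling to the full protocol. The 70/30 split and the surgeon differences have no source in the document. They illustrate a route left open, not one shown to be used.

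A third tempting reading is that surgeon was left out of the randomisation and the models because experience was thought to exclude bias. The article never links the two.

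Finally, having both surgeons competent in both techniques is a real safeguard. It avoids a design in which each arm has its own operator, and the sentence may be aimed at that. The gain from adjustment is also small, and stratifying by surgeon in a single-centre trial of 110 is a preference rather than a correction of an error.

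All of this limits the consequence. It does not make the stated inference valid, and it does not explain why an itemised covariate list for an accuracy outcome omits the operator. Both are things the article states, not details it leaves elsewhere.

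**Conclusion.** The point holds in limited form. The article asserts that there will be no bias on grounds that cannot establish it, and nothing in the described randomisation or covariate list makes up for that. With surgeon independent of allocation, the cost is chance imbalance and, under an assumed 20-point surgeon difference, about 1.7 points of power forgone (83.6% minus 81.9%). Systematic confounding is conditional on the surgeon being chosen after the technique is known. Under the assumed 70/30 versus 30/70 shares it would amount to 4 to 12 points. The facts about the text are firm; every figure for the surgeon effect rests on assumed shares and differences. This is worth correcting because correction is cheap, but it is not a flaw that by itself undermines the primary comparison.

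**What to change.** - Delete the claim under Interventions that experience excludes bias. Say only that both surgeons are experienced in both techniques.
- Record the operating surgeon for every patient and include surgeon as a prespecified fixed term in the linear and logistic models, exempt from the 10% change rule. That rule could drop a strongly prognostic surgeon effect whenever the shares happen to be similar.
- If recruitment is still open, fix and document the operating surgeon before the envelope is opened. This closes the systematic route at its source. Stratifying the remaining envelopes by surgeon is optional.
- If recruitment is complete, the model term can still be added, provided the surgeon can be identified from the operative records.

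Cost: one degree of freedom per model, about half a point of power if the surgeons do not differ (81.8% to 81.2%), and a second set of envelopes if stratification is chosen. The sample size is unchanged.

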#### Combined wedge osteotomy (CWO)

For the combined wedge HTO, instrumentation of Allopro (Zimmer; Winterthur, Switzerland) will be used. The common peroneal nerve will be exposed and snared with a nerve band. Next, the anterior part of the proximal fibular head (anterior part of the proximal tibiofibular syndesmosis) will be resected. The proximal osteotomy is performed using an oscillating saw up to the center of the tibial head, 2 cm distally from the joint line. After positioning the aiming device in the first osteotomy, a second distal osteotomy is made, which results in a laterally-based bone wedge. The bone wedge is removed. The distal part of the tibia is placed in valgus position, so the lateral part of the osteotomy closes and the medial part of the osteotomy opens. The center of the valgisation is the center of the tibial head. The half bone wedge is placed back in the gap opened on the medial side. The osteotomy is secured with staples, two on the lateral side and one on the medial side. At the end of the procedure a fasciotomy of the anterior compartment will be performed to prevent compartment syndrome.

#### Lateral closing wedge osteotomy (LCW)

For the lateral closing wedge HTO, instrumentation of Allopro (Zimmer; Winterthur, Switzerland) will be used. The common peroneal nerve will be exposed and snared with a nerve band. Next, the anterior part of the proximal fibular head (anterior part of the proximal tibiofibular syndesmosis) will be resected. The osteotomy will be made and the wedge taken out. The osteotomy will be fixated with two staples. At the end of the procedure a fasciotomy of the anterior compartment will be performed to prevent compartment syndrome.

The postoperative treatment for both HTO techniques consists of a pressure bandage for 24 hours and cast immobilization until removal of the stitches, followed by flexion-extension brace protection and 50% weight bearing for 6 weeks. After this period, weight bearing can be built up to 100% based on the pain sensation of the patient, brace use can be reduced to no brace, and physical therapy will be started.

### Main study parameter/endpoint

Primary outcome measure is the accuracy and preservation correction of the technique, defined by achievement of an overcorrection of 4° valgus one year after surgery as measured by the hip-knee-ankle (HKA) angle. The continuous differences in achievement of a valgus overcorrection and the deviation from 4° valgus will be determined, as well as dichotomous outcome and achievement of a 0-6° valgus alignment .

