### Study procedures

Preoperatively as well as six weeks, six months and one year postoperatively, patients will visit the outpatient clinic. Routine physical examination will be performed by the orthopedic surgeon.

Primary outcome measure–achievement of an overcorrection of 4° valgus alignment / hip-knee-ankle angle (HKA, in degrees)–will be measured after one year on a whole-leg radiograph (WLR) standing on one leg. The continuous differences in achievement of a valgus overcorrection and the deviation from 4° valgus are determined. A dichotomous outcome is achievement of a 2-6° valgus alignment.

Secondary outcome measures, posterior tibial slope (Moore-Harvey and Dejour-Bonin), patellar height (Insall-Salvati and Caton Index) and difference in leg length (cm) one year after surgery will be obtained. Pain severity (VAS; range 0–10), knee function and quality of life (KOOS), and walking distance (km) six weeks, three months, six months and one year after surgery will also be obtained.

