### Sample size calculation

The sample size was calculated based on an expected increase of the success rate from 60% in the closed wedge HTO to 85% in the combined wedge HTO. A successful operative result is defined as achievement of a 2-6° valgus alignment. To detect such a difference with α= 0.05 and a power of 80%, we need to include 50 patients in each study group. To adjust for possible loss to follow-up, a total of 110 patients will be included in the study.

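### The primary outcome is given in several versions (valgus angle, deviation from 4°, and a range stated as 0-6° or 2-6°) with none named as confirmatory, although only 2-6° success is powered

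*Protocol article*

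**What the plan says.** All references are to the protocol article.

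- **Main study parameter/endpoint** describes the primary outcome as accuracy and preservation of correction, "defined by achievement of an overcorrection of 4° valgus one year after surgery as measured by the hip-knee-ankle (HKA) angle". It then splits this into continuous measures and a dichotomous part, "The continuous differences in achievement of a valgus overcorrection and the deviation from 4° valgus will be determined, as well as dichotomous outcome", the latter reading in full "as well as dichotomous outcome and achievement of a 0-6° valgus alignment".
- **Study procedures** repeats this structure under the primary outcome, but with another range: "A dichotomous outcome is achievement of a 2-6° valgus alignment".
- **Abstract (Methods/design)** gives only the 4° overcorrection at one year and does not say which version is analysed.
- **Secondary study parameters/endpoints** lists slope, patellar height, leg length, pain, function and walking distance. None of the alignment measures appears there, so all of them sit in the primary tier.
- **Sample size calculation** uses one version only: "A successful operative result is defined as achievement of a 2-6° valgus alignment". It takes 60% success for the closing wedge and 85% for the combined wedge, with α = 0.05, 80% power and 50 per group.
- **Statistics** assigns postoperative alignment to linear regression and dichotomous outcomes to logistic regression, and closes with a general rule: "a p-value of 0.05 is considered statistically significant". Deviation from 4° is not named there as a separate dependent variable.

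**The concern.** A confirmatory trial needs one stated variable whose result decides the question, or a stated rule for combining several. Here the primary tier holds at least three candidates and the text does not choose among them. Two things are at stake.

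First, the 5% error rate used for the sample size holds only if one pre-specified test decides. If the choice stays open until the data are in, the real rate is higher.

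Second, the versions answer different questions and can disagree. The hypothesis is about more accurate correction, and the Interventions section says that surgery aims at 4° in every patient. Two techniques could share a mean angle and differ only in spread. Mean HKA would then show nothing, while deviation and 2-6° success would differ. Conversely, arms with means of 3° and 5° and equal spread would differ in mean HKA, yet have the same average deviation from 4° and, if the distributions are symmetric, the same 2-6° success rate. The document gives no reading for either pattern.

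**Working it through.** **1. The plan's own figure.** Inputs from Sample size calculation: p₁ = 0.60, p₂ = 0.85, α = 0.05, power 80%. Sidedness is not stated, so two-sided is tried first. Pooled-variance formula without continuity correction:

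n = [z₀.₉₇₅·√(2p̄(1−p̄)) + z₀.₈₀·√(p₁(1−p₁) + p₂(1−p₂))]² / (p₂−p₁)²

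With p̄ = 0.725: 1.96·√0.39875 = 1.2377; 0.8416·√(0.24 + 0.1275) = 0.5102; (1.2377 + 0.5102)² / 0.0625 = 48.9, so 49 per group. The stated 50 is reproduced, with 80.9% power at 50 and 84.5% at 55 (half of 110). The sample size is correct for 2-6° success as a single two-sided test.

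**2. How far the versions can diverge.** Assume normal HKA with both arms centred on 4°. A 60% chance of lying within ±2° needs an SD of about 2.38° (2/2.38 = 0.84), and 85% needs about 1.39° (2/1.39 = 1.44). The planned 60% versus 85% could therefore arise with no difference at all in mean HKA.

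**3. False-positive risk if any one of several tests counts.** Independent tests would give 1 − 0.95² = 9.75% for two and 1 − 0.95³ = 14.3% for three. All versions come from one angle, so they are correlated and simulation is needed. The setup was 50 per arm with the same normal HKA distribution in both arms, a t-test on HKA, a t-test on |HKA − 4°| and a two-proportion test on 2-6°, with 60,000 replicates per row. The document gives no mean or SD for HKA, so both are assumptions.

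| Mean, SD (°) | 2-6° success | Any of three | Angle or 2-6° | Deviation or 2-6° |
|---|---|---|---|---|
| 4, 2.376 | 60% | 12.4% | 10.0% | 7.8% |
| 4, 1.77 | 74% | 12.4% | 9.8% | 7.8% |
| 4, 1.39 | 85% | 13.1% | 10.2% | 8.5% |
| 3.5, 2 | 67% | 11.9% | 9.5% | 7.7% |
| 3, 1.8 | 66% | 11.1% | 9.1% | 7.7% |
| 3, 1.2 | 79% | 10.6% | 8.6% | 8.1% |
| 2.5, 1.5 | 62% | 9.6% | 8.2% | 7.5% |
| 2.3, 1.2 | 60% | 8.8% | 7.9% | 7.7% |

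A second set of runs (40,000 replicates) gave 12.2-12.8% at mean 4° and 9.1% at mean 1°, SD 2°. The three-test risk is thus about 9-13%, or 1.8 to 2.6 times the nominal 5%. With the angle and 2-6° success only, it is about 8-10%.

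**4. Cost of keeping several co-equal primaries.** Bonferroni at 0.05/3 = 0.0167 needs 66 per group for 80% power on 2-6° success. Power would be 66.4% at 50 and 71.4% at 55. With two primaries (0.025) it needs 60 per group, with power 71.9% at 50 and 76.5% at 55.

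**The case against.** The strongest defence is that the protocol already points to its anchor. Sample size calculation defines a successful result as 2-6° and powers the trial on it, and Study procedures uses the same range. Sizing a trial on one version is not an error, and a testing order is commonly left to an analysis plan, which is not shown here. This stands as far as it goes: the absence of a multiplicity procedure is not the point. But which variable is primary is for the protocol to say. The endpoint section does speak to it, and names several, with a dichotomous range that is not the powered one.

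Three stronger readings are tempting and are not supported:

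- **That each version will be tested at 0.05.** The endpoint section says only that the continuous measures will be determined. The Statistics section names postoperative alignment and dichotomous outcomes but not deviation from 4°, and its threshold is a general one. Two alignment tests are as defensible a count as three.
- **That the false-positive risk more than doubles.** This needs all three tests, one-year angles centred fairly near 4°, and a rule that any one significant result makes the trial positive. The document neither states nor excludes such a rule. Because the endpoint also covers preservation of correction, a one-year mean away from the target is plausible, and the figure then falls towards 9%.
- **That 0-6° is a further planned test.** It reads more naturally as a conflict over the same dichotomous outcome, to be reconciled.

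The simulation also uses unadjusted tests, whereas the plan has multivariable models with covariates chosen by a 10% change rule. The percentages are therefore indicative.

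**Conclusion.** The point holds in this form: several versions of the primary outcome are listed, none is designated, the dichotomous range is inconsistent, and only 2-6° success is powered. That much rests on the text alone and is firm.

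The size is conditional. It is roughly 9-13% against the stated 5% if all three versions are tested and any one suffices, and 12-13% if both arms centre on 4°. It is about 8-10% if only the angle and 2-6° success are tested. These figures assume normal HKA distributions with means and SDs that the document does not supply. The sample size itself is not wrong. This should be corrected, but it needs no redesign.

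**What to change.** - In the Abstract (Methods/design), Main study parameter/endpoint and Study procedures, name one primary endpoint: HKA within 2-6° valgus at one year, compared between groups at two-sided 0.05. This is the version already used for the 50-per-group calculation.
- Reconcile the 0-6° range in Main study parameter/endpoint with the 2-6° range in Study procedures and Sample size calculation.
- Label mean HKA and deviation from 4° as secondary or supportive. State that the deviation is absolute if that is what is meant.

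The cost is a short wording change in three places, with no added patients: type I error for the primary test stays at 5% and power at 50 per group stays at 80.9%. The downside is that the continuous results, although still reported, can no longer by themselves make the trial positive. If co-equal primaries are preferred, the price is the larger sample or lower power shown in step 4 of the working.
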